## 2 Background

### 2.1 Introduction

Hospital acquired venous thromboembolism (VTE) has been identified as an increasing cause of morbidity and mortality in pediatric populations. While overall a rare complication in children, annual rates have been increasing, with a 70% increase in pediatric VTE demonstrated from 2001 to 2007. Despite the increasing incidence, many treatment recommendations for pediatric VTE have been extrapolated from adult data. Because children with VTE experience longer hospital stays, increased medical costs, and subsequent medical complications, it is important to identify patients early who are at increased risk. Given these risks, it is imperative that we develop a more personalized approach to identify children at highest risk for VTE so that focused interventions can be initiated.

Prior risk prediction models have been developed to evaluate pediatric patients at risk for VTE development. These models, however, suffer from small samples sizes (<1000 patient observations) and typically are not prospectively validated. Since risk prediction models have been shown to identify patients at high-risk for VTE events

better than physician judgement alone, our goal is to develop and validate a predictive model of pediatric thrombosis using a large, single center, retrospective cohort.

## 2.2 Model Development

We evaluated data from 111,352 admissions to Vanderbilt Children's Hospital from 1/1/2010 to 10/31/2017. Cases were identified from ICD9/10 codes and a subset of these records were reviewed for accuracy. Potential covariates were identified from known pediatric risk factors for VTE development prior to data collection, and the corresponding clinical data were electronically extracted through the Vanderbilt Research Derivative. Logistic regression was used to test the association of potential risk factors with development of VTE. Variable inclusion in the final model was based on data reduction methods including univariate analysis significance, availability in routine medical records, clinical expertise, and assessment of collinearity between variables. The model was validated using an internal bootstrap calibration.

We identified 110,537 controls and 815 cases within the cohort. The most significant variables for developing VTE were a history of thrombosis (OR 8.7, 95% CI 6.6 – 11.3,  $p < 0.01$ ), presence of a central venous line (OR 4.9, 95% CI 4.0 – 5.8,  $p < 0.01$ ), and cardiology consultation (OR 4.0, 95% CI 3.3 – 4.8,  $p < 0.01$ ). Additional significant variables included whether a blood gas was performed, whether the patient had an infectious diseases consultation, patient age, mean corpuscular hemoglobin concentration (MCHC), red cell distribution width (RDW), and lactate. We selected these 11 final variables for use in the model, which yielded excellent discriminatory power (C-statistic = 0.907 in the model development cohort).

## 3 Rationale and Specific Aims

We have developed a general electronic health record (EHR)-based pediatric risk prediction model that can identify pediatric patients upon admission who are at higher than average risk for developing a VTE. We plan to evaluate whether using this VTE model risk score increases the number of high-risk patients screened by the VTE research team. The VTE research team will then consider various clinical recommendations, including potential prophylactic anticoagulation. We hypothesize that using this clinical support tool will lead to an overall reduction in the number of pediatric VTE seen in our institution.

## 4 Eligibility Criteria

Inclusion criteria:

1. All pediatric patients 0-21 years of age who are admitted to an inpatient unit of Vanderbilt Children's Hospital (VCH) will be included in the study.

Subjects must not meet any of the following exclusion criteria:

1. Receiving prophylactic or therapeutic dosing of anticoagulants, including enoxaparin, warfarin, bivalirudin, apixaban, rivaroxaban, dabigatran, and edoxaban.
2. Patients admitted under "observation status"

## **5 Enrollment/Randomization**

### **5.1 Enrollment**

All patients admitted to the VCH during the study period will be enrolled if they meet the eligibility criteria listed above. We are requesting waiver of consent for this trial due to the impracticality of obtaining consent for every pediatric patient admitted to VCH and overall minimal risk to participants.

### **5.2 Randomization**

Patients will be randomized 1:1 to the intervention or control arms upon admission via an automatic process built into the electronic health record. Both arms will continue to receive local standard of care practice for VTE prophylaxis.

## **6 Study Procedures**

### **6.1 Intervention and Control Arms**

Patients will be enrolled into the study upon admission to Vanderbilt Children's Hospital. All patients in both arms will have a VTE risk percentage calculated based on their values in the logistic regression model. This will initially be calculated at the time of admission and only be available in real-time to the study team for the intervention arm.

### **6.2 Intervention Arm**

Patients in the intervention arm will have their VTE risk prediction scores presented to the study team daily on weekdays via Epic report, which will list patients in descending order of risk severity for review by the VTE research team each weekday. Starting with the highest risk patients, the VTE research team will review each patient and clinical situation, and then the VTE research team will directly discuss risks/benefits

of prophylactic anticoagulation with the admitting team. Patients with a risk score  $<2.5\%$  will not be reviewed, and we anticipate most of the intervention arm patients will fall into this category (based on our previous data, we anticipate  $>90\%$  of all patients will score  $<2.5\%$ ). The VTE risk report will be re-calculated based on updated EHR data every day at midnight.

### **6.3 Control Arm**

Patients randomized to the control arm will continue to receive Vanderbilt Children's Hospital standard of care anticoagulation practice, which is at the discretion of the admitting team. In general, nearly no pediatric patients are offered prophylactic anticoagulation unless a previous VTE has been identified. This currently is at the discretion of the provider and no risk scoring is used. VTE risk prediction scores will be calculated and stored for analysis, these will not be visible to the study team in real time.

### **6.4 Outcomes**

### **6.5 Primary Outcomes**

The primary outcome will be to determine whether the number of VTE events is lower in the intervention arm than the control arm. The endpoint measure will be calculated as the frequency of VTE events per hospital admission encounter per arm.

VTE outcomes will be tracked in both arms of the study on a monthly basis. The radiology coordinator will provide a report of all pediatric radiology studies completed in the prior month. The VTE research team will filter the data based on the location that the imaging was performed (such as inpatient at VCH) and type of radiology study to best identify VTEs (such as ultrasounds with doppler and CT-angiograms). We will then review the filtered report to identify the MRN of patients and the date of the VTEs that were identified during that time period.

An additional data sample will be obtained from the EMR one month after enrollment completion to assess ICD9/ICD10 codes for acute VTE (utilizing codes established during model development and validation) during the trial period to further confirm all VTE events were appropriately captured in the monthly reports.

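### The team that delivers the intervention also decides, unmasked, which scans count as primary VTE events, and no rule requires a counted VTE to be new after randomization

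*Protocol*

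**What the plan says.** **Endpoint.** Protocol Section 6.5: "The endpoint measure will be calculated as the frequency of VTE events per hospital admission encounter per arm". Section 10.1 compares the arms by an unadjusted risk difference and a two-sided Pearson chi-square test at 0.05.

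**Who finds the events.** In Section 6.5 the radiology coordinator supplies a monthly report of all pediatric studies. The VTE research team filters it by imaging location and study type, both given only by example. Then: "We will then review the filtered report to identify the MRN of patients and the date of the VTEs that were identified". One month after enrollment ends, an ICD pull for acute VTE checks that the monthly reports were complete.

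**Who delivers the intervention.** Section 6.1 says risk scores will "only be available in real-time to the study team for the intervention arm". In Section 6.2 the team works down the ranked list each weekday, and "the VTE research team will directly discuss risks/benefits" of prophylaxis with the admitting team.

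**Which VTE is the target.** Section 2.1 opens: "Hospital acquired venous thromboembolism (VTE) has been identified as an increasing cause of morbidity and mortality in pediatric populations". Section 3 describes a model that flags, at admission, children at raised risk of developing a VTE. Section 5.2 randomizes at admission. Section 6.5 records a date for each VTE, but no rule uses it.

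**The concern.** There are two separate gaps, and they differ in kind.

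1. **Classification is not masked.** The people who advised on the highest-risk intervention patients later decide, with MRNs in view, which studies to keep and which are events. Those are the patients most likely to have events, so the readers can recognize many intervention-arm cases. Whether a finding is old or new, incidental or equivocal is left to their judgment. An error that depends on arm biases the primary risk difference, in either direction, and a larger trial makes a false conclusion more likely.

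2. **There is no onset rule.** A child who arrives with an undiagnosed clot and is scanned as an inpatient has been randomized and, as Section 6.5 is written, can be counted. Preventive advice cannot avert that event. Randomization balances such events between arms, so they cost power and shrink the relative effect but create no false difference.

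**Working it through.** **Inputs.** Control risk 1%, intervention risk 0.595%, 7,500 per group, 80% power, and 15,000 to 45,000 patients at 1:1, hence at most 22,500 per arm (Section 10.2). Two-sided 0.05, Pearson chi-square (Section 10.1). Two inputs are assumptions, because the documents give neither: the share *m* of intervention-arm events not counted (5%, 10%), and the share *f* of counted events already present at admission (10%, 20%, 30%).

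**Formula.** With d = p1 − p2 and pb = (p1 + p2)/2:

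- SE0 = √[2·pb(1 − pb)/n]
- SE1 = √[(p1(1 − p1) + p2(1 − p2))/n]
- P(reject) = Φ[(d − 1.96·SE0)/SE1] + Φ[(−d − 1.96·SE0)/SE1]

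**Step 1: the plan's own figure.** p1 = 0.01, p2 = 0.00595, n = 7,500: d = 0.00405, SE0 = SE1 = 0.001452 to that precision, so power = 0.796. The stated 80% reproduces. The relative reduction is 1 − 0.595 = 40.5%.

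**Step 2: unmasked classification under no true effect.** The true risk is 1% in both arms, but the intervention arm is counted at 0.01(1 − m).

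| m | n per arm | Counted events, control vs intervention | d | SE0 | P(p < 0.05) |
|---|---|---|---|---|---|
| 5% | 7,500 | 75 vs 71.25 | 0.0005 | 0.001605 | 6.1% |
| 10% | 7,500 | 75 vs 67.5 | 0.0010 | 0.001584 | 9.7% |
| 5% | 22,500 | 225 vs 213.75 | 0.0005 | 0.000926 | 8.4% |
| 10% | 22,500 | 225 vs 202.5 | 0.0010 | 0.000915 | 19.4% |

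At 7,500 per arm, these shares amount to about 4 to 8 events. Tripling the sample raises the error rate.

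**Step 3: dilution by clots present at admission.** Keep the counted control risk at 1% and apply the 40.5% reduction only to the rest: p2 = 0.01[f + (1 − f)·0.595].

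| f | p2 | Power, 7,500 per arm | Power, 22,500 per arm | Power, 7,500 per arm, counting only the other events |
|---|---|---|---|---|
| 10% | 0.636% | 0.70 | 0.99 | 0.75 |
| 20% | 0.676% | 0.59 | 0.965 | 0.70 |
| 30% | 0.717% | 0.47 | 0.90 | 0.64 |

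The last column uses (1 − f)·1% vs (1 − f)·0.595%. Counting fewer but preventable events gives more power in each row. A larger sample largely repairs dilution, but it does not repair Step 2.

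**The case against.** **On masking.** The team reads a report supplied by the radiology coordinator, not images. The protocol does not say that arm appears on it, control-arm scores are hidden in real time, and the ICD check may recover omitted events. This limits the scope for bias but does not remove it. MRNs are in view, the readers know the intervention patients they advised on, the filter is open-ended, and no rule settles a disagreement between the two sources. The 5% to 10% is illustrative. Nothing in the protocol suggests that events will in fact be misclassified.

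**On onset.** A reader might infer that the endpoint deliberately counts clots present at admission. The protocol does not say so; it is silent. The ICD pull is limited to acute VTE, and the anticoagulant exclusion and the inpatient-location filter remove some known clots. The hypothesis in Section 3 is also worded broadly, as fewer pediatric VTE at the institution, so an inclusive count is a defensible choice. What stands is that the choice is not stated and the recorded date is not used.

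**On power.** A reader might take the fall to 0.47 as a demonstrated shortfall. It is not: the share is assumed, the planned 0.595% may already allow for events that cannot be prevented, and Section 10.2 permits up to 45,000 patients.

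**On eligibility.** A reader might infer that heparin-treated children can enter, because Section 4 does not name heparin: "Receiving prophylactic or therapeutic dosing of anticoagulants, including enoxaparin, warfarin, bivalirudin, apixaban, rivaroxaban, dabigatran, and edoxaban". The agents are introduced as examples of anticoagulants, so the text does not support that.

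**Conclusion.** The point holds in two parts of unequal weight.

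The main part is unmasked classification. Section 6.5 itself fixes who identifies events, and it is the team that delivers the intervention. The likely size of the bias is unknown. Under the stated illustration, type I error is 6.1% to 9.7% at the minimum size and 8.4% to 19.4% at the maximum. The lack of masking is inferred from the assigned roles and from the absence of any masking step.

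The lesser part is the missing onset rule. It can weaken the relative effect and the power, but it does not bias the comparison between arms. The Step 3 figures rest on an assumed 10% to 30% share and on the 40.5% reduction applying only to preventable events. They show direction and do not estimate this trial's power.

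**What to change.** **Masking (Section 6.5).** Fix the list of study types and locations before the first report is filtered. Have arm and MRN replaced by a study code in the monthly report before the VTE research team sees it. Classify from the report text, lock the classification, and only then link to arm. Mask events found only by the ICD check in the same way.

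**Event definition (Section 6.5).** Define the primary event as a new VTE first diagnosed after randomization. Use the date already collected and an objective rule, including how very early diagnoses are handled, applied identically in both arms once the masked classification is done. Two things should stay out of the rule. Chart documentation that a clot was already present should not decide the matter, because the extra chart review in the intervention arm could produce more of it there and turn balanced dilution into differential exclusion. Recurrence at the same site should not be excluded automatically, because prior thrombosis is the strongest predictor in Section 2.2 (OR 8.7) and true recurrences would be lost. Report all VTE as a sensitivity analysis.

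**Cost.** A small data-handling step on an existing report, with no additional reader, and slightly fewer counted primary events.

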## 6.6 Secondary Outcomes

Secondary outcomes will include:

1. Total number of patients, without contraindications to anticoagulant medications as described by the prescriber information for heparin and enoxaparin determined by the consulting hematologist, who are begun on prophylactic anticoagulation, by study arm
2. Total number of high-risk patients, without contraindications to anticoagulant medications as described by the prescriber information for heparin and enoxaparin determined by the consulting hematologist, who are begun on prophylactic anticoagulation, by study arm
3. Total number of patients, without contraindications to anticoagulant medications as described by the prescriber information for heparin and enoxaparin determined by the consulting hematologist, who are begun on anticoagulation medications compared to the total number of patients for which initiation of anticoagulation was recommended by the VTE research team.
4. Frequency of bleeding-related adverse events per number of patients begun on prophylactic anticoagulation, scored using the modified WHO bleeding scale, by study arm, during hospitalization

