## 7 Risks of Intervention

The primary focus of our study is to determine if a VTE risk prediction tool increases the number of high-risk patients reviewed by the pediatric VTE research team. The majority of the patients in the study will be considered low risk (based on previous data, we anticipate >90% of all patients to fall into this category). High-risk patients in the intervention arm will receive an additional chart review and subspecialty expertise. Part of that subspecialty expertise may include recommendations to initiate prophylactic anticoagulation. The use of pharmacologic anticoagulation is the standard of care among peer pediatric institutions and among adult hospitalized patients (including at Vanderbilt University Medical Center). In fact, nearly all adult patients are provided some type of VTE prophylaxis upon admission. The decision to start patients on prophylactic anticoagulation is complex and involves consideration of the patient's clinical status and review for possible contraindications. We would not consider patients for anticoagulation with severe bleeding disorders, clinically significant hemorrhage, severe renal dysfunction, or anything in the opinion of the investigator that would jeopardize the safety of the subject. Pharmacologic prophylaxis is performed using various anticoagulant medications, most commonly with heparin or enoxaparin.

These drugs are commonly used, FDA-approved for anticoagulation, and considered to be safe; side effects of these medications include injection site reactions, bleeding, and rarely, thrombocytopenia. In several studies of pediatric VTE pharmacologic prophylaxis, there were very few bleeding episodes reported.

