## 10 Statistical Considerations

### 10.1 Statistical Analysis Plan

Primary analyses will be conducted at the encounter level, while secondary analyses will be conducted at the patient level (patients can potentially experience multiple encounters during the study period).

The rate of VTE events (primary outcome), the proportion of patients receiving prophylactic anticoagulation (secondary outcome), and the rate of bleeding-related adverse events (secondary outcome) will be compared between the intervention and control arms using unadjusted risk differences with 95% confidence intervals. We have not specified *a priori* any adjustment variables to include in multivariable models. Any variable with a clinically meaningful imbalance between the intervention and control groups will be adjusted for in multivariable regression models; given the large sample size we do not anticipate any such imbalances. For the primary outcome, a two-sided p-value (obtained from Pearson's chi-square test) of  $< 0.05$  will indicate statistical significance. Secondary subgroup analyses will be performed by patient gender, risk of VTE, primary diagnoses, surgical vs. nonsurgical, and consultants involved.

Primary analyses will be conducted by intention-to-treat; secondary analyses will be as treated, considering whether treatment recommendations were followed by the admitting team. Secondary as-treated analyses will be performed among the strata of high-risk patients (predicted probability  $\geq 0.025$ ) randomized to usual care, to the intervention but treatment recommendations were not followed, and to the intervention and treatment recommendations were followed.

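### The between-arm bleeding comparison is divided by patients begun on prophylaxis, a number the intervention itself changes, so it does not estimate the tool's randomized effect on bleeding

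*Protocol*

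**What the plan says.** Section 6.6, item 4, sets the outcome and its denominator: "Frequency of bleeding-related adverse events per number of patients begun on prophylactic anticoagulation, scored using the modified WHO bleeding scale, by study arm". Section 10.1 says that this rate "will be compared between the intervention and control arms using unadjusted risk differences with 95% confidence intervals". It gives no bleeding rate over all randomized patients or encounters.

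Four other statements bear on the denominator:

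- Section 7 describes how the intervention acts: "Part of that subspecialty expertise may include recommendations to initiate prophylactic anticoagulation".
- Section 6.3 says of usual care that "nearly no pediatric patients are offered prophylactic anticoagulation unless a previous VTE has been identified".
- Section 4 excludes children already "Receiving prophylactic or therapeutic dosing of anticoagulants".
- Section 6.6, items 1 and 2, count starts of prophylaxis by arm as outcomes in their own right.

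Section 10.1 also states: "Primary analyses will be conducted by intention-to-treat; secondary analyses will be as treated, considering whether treatment recommendations were followed by the admitting team". The primary outcome, by contrast, is VTE events per admission encounter in each arm (Section 6.5).

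**The concern.** Bleeding is the trial's only comparative safety outcome, and Section 8.1 limits adverse event collection to coagulation and hemostasis events. If the tool causes bleeding, it does so mainly because more children receive an anticoagulant. Dividing by the number who received one takes that route out of the comparison. It also compares two groups that randomization did not form: children started after a high score and a specialist discussion, and children started at the admitting team's discretion, chiefly because of a previous VTE.

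At stake is whether the report can set harm beside benefit. The primary outcome is per encounter and includes everyone randomized. The bleeding outcome is per treated child and includes a subset whose size differs by arm.

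**Working it through.** **The plan's own figure.** The protocol gives no number for bleeding. Its one sample-size figure, 80% power for 1% against 0.595% with 7,500 per arm, reproduces. With pooled variance under the null, z = (0.00405·√7500 − 1.96·√(2·0.007975·0.992025)) / √(0.01·0.99 + 0.00595·0.99405) = (0.3507 − 0.2465)/0.1258 = 0.83, which is 79.6% power. It has no bearing on bleeding.

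**What the measure estimates.** Let n_I and n_C be the children begun on prophylaxis in each arm, and r_I and r_C their bleeding risks.

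1. Only bleeds in treated children counted, r_I = r_C: the expected difference is r_I − r_C = 0 for any n_I and n_C.
2. Only bleeds in treated children counted, r_I ≠ r_C: the difference mixes any effect of the tool with how the two treated groups were selected.
3. All bleeds in the arm counted (item 4 does not restrict the numerator): the smaller n_C inflates the control rate.

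None of these is the effect of randomization on bleeding.

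**Illustration.** From the documents: 7,500 per arm, and more than 90% of children scoring below 2.5%. Assumed, and not in the protocol: 6% to 9% high-risk (450 to 675 per arm), 50% of them started in the intervention arm and 5% in the control arm, and bleeding in 3% of treated and 1% of untreated children.

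| Quantity | 450 high-risk | 675 high-risk |
|---|---|---|
| Treated, intervention vs control | 225 vs 22.5 | 337.5 vs 33.75 |
| Planned measure, treated bleeds only | 3% vs 3% | 3% vs 3% |
| 95% half-width, 1.96·√(0.03·0.97·(1/n_I + 1/n_C)) | 7.4 points | 6.0 points |
| Bleeds in all high-risk children | 9.0 vs 4.95 | 13.5 vs 7.4 |
| Risk difference, all high-risk | 0.9 ± 1.6 points | 0.9 ± 1.3 points |
| Bleeds, all randomized (low-risk also at 1%) | 79.5 vs 75.5 | 81.8 vs 75.7 |
| Risk difference, all randomized | 0.05 ± 0.32 points | 0.08 ± 0.33 points |

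For 450 high-risk children the bleeds are 225·0.03 + 225·0.01 = 9.0 and 22.5·0.03 + 427.5·0.01 = 4.95. If all of these were divided by treated children (case 3), the rates would be 9.0/225 = 4% and 4.95/22.5 = 22%, which reverses the direction of the excess.

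**Sensitivity to uptake.** With the other assumptions fixed, the relative excess among high-risk children is about 9% at 10% uptake (5.4 vs 4.95), 27% at 20% (6.3 vs 4.95) and 82% at 50% (9.0 vs 4.95). The per-treated difference is 0 at each.

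**A second set of assumptions.** Take 5% to 10% high-risk, 20% to 50% of them started, background starts of 0.1% to 1% of each arm, and bleeding in 1% to 3% of treated children. The control denominator is then about 8 to 75 children, against about 83 to 450 in the intervention arm. The chance of no bleed at all among treated controls is 10% to 93%. The half-width is 2.4 to 12.8 points, wider than the assumed bleeding risk in every scenario. With so few events these normal-approximation widths are rough.

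**The case against.** The strongest counter-case has four parts.

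- **The alternative is also weak.** Over all encounters the difference is diluted to 0.05 to 0.08 points against about ±0.32, and the high-risk intervals also include zero. This stands: the proposed comparison may not detect an excess. It is nevertheless protected by randomization, and in high-risk children its interval is about a fifth as wide as the planned one.
- **Other planned results help.** Items 1 and 2 show starts by arm, so a careful reader could see that more children were treated. If the numerator is treated children's bleeds, it could be re-divided by the number randomized. Section 10.1 also plans strata of high-risk patients that include all high-risk controls, though it does not name the outcomes covered. This softens the problem, but leaves the randomized comparison to be reconstructed by the reader.
- **Safety oversight exists.** Grade 3 and 4 bleeds are serious adverse events (Section 8.2), and the safety monitoring committee sees event reports and outcome data (Section 8.5). This is monitoring and does not define a between-arm estimate.
- **The outcome is secondary.** Section 10.1 sets a significance threshold for the primary outcome only. This stands and limits the severity.

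A reader might infer more: that extra bleeding always cancels out, that the control denominator is practically empty, or that an 82% excess would be hidden. The documents do not support these. Cancelling needs equal per-treated risk and a numerator restricted to treated children. Section 6.3 gives no count, and new starts in children with a previous VTE remain in the denominator. The 82% comes from one assumed uptake.

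**Conclusion.** The point holds in this form: as defined, the between-arm bleeding comparison conditions on a post-randomization quantity that the intervention is designed to raise, and under no reading of its numerator does it estimate the tool's randomized effect on bleeding. That conclusion rests on the protocol text alone. The sizes rest on the assumed high-risk share, uptake and bleeding rates: an expected difference of 0 with ±6 to 7 points for the planned measure under the equal-risk reading, against about 0.9 points with ±1.3 to 1.6 in high-risk children by intention-to-treat, both at the minimum enrollment of 7,500 per arm. It should be fixed, but as a secondary-outcome matter. It does not follow that the trial must report no difference in bleeding, or that harm would go unseen.

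**What to change.** In Sections 6.6 (item 4) and 10.1:

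1. Make the between-arm safety comparison intention-to-treat: encounters with a bleed over all randomized encounters in each arm, as a risk difference with 95% confidence interval. State that it is at encounter level, to match the primary outcome, because Section 10.1 places secondary analyses at patient level.
2. Add, as the more informative comparison, the same measure among all encounters with an admission score of at least 2.5% in each arm. Control scores are already stored (Section 6.3). Use the admission score because later daily scores can reflect care given after randomization; children who cross the threshold later then fall outside this subset.
3. Ascertain bleeds identically in both arms, for example by adding bleeding and transfusion codes to the EMR pull planned one month after enrollment ends (Section 6.5). Limit the code-based comparison to what codes can identify, such as severe or transfused bleeds; codes cannot assign WHO grade 2.
4. Keep the rate per treated child as a descriptive figure by arm, without a between-arm comparison, and state whose bleeds its numerator counts.

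The cost is wording and extra codes in an extract already planned. Code-based capture will miss mild bleeds, and the intervals may still include zero. If the size of the possible excess is quoted, show it as a range over assumed uptake.
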